#### Secondary Process Outcomes

2.9.3

Proportion of patients with new pleural infection defined as any positive pleural fluid culture of any fungi or bacteria except pre‐defined contaminants being coagulase negative Staphylococci, Enterococci, and *Corynebacterium* species in any pleural fluid sampling conducted after 24 h from randomisation up until 90 days after randomisation.PaO_2_:FiO_2_ ratio in the arterial blood gas analysis (ABG) conducted in ICU closest to 24 and 72 h after randomisation. The FiO_2_ in open systems will be estimated from pre‐specified conversion tables (see Table 2)pH in the ABG conducted in ICU closest to 24 and 72 h after randomisation.PaCO_2_ in the ABG conducted in ICU closest to 24 and 72 h after randomisation.

**TABLE 2 aas70233-tbl-0002:** Conversion tables for calculating FiO_2_ in open systems.

Nasal cannula^a^											
Oxygen flow	0 L/min	1 L/min	2 L/min	3 L/min	4 L/min	5 L/min	6 L/min	8 L/min	10 L/min	12 L/min	14 L/min
FiO_2_	0.21	0.27	0.33	0.37	0.40	0.44	0.48	0.55	0.62	0.64	0.66

High‐flow humidified oxygen^b^																	
Total flow	Percentages represent oxygen concentration in the gas mixture, fractions the corresponding FiO_2_																
	21%	25%	30%	35%	40%	45%	50%	55%	60%	65%	70%	75%	80%	85%	90%	95%	100%
15 L/min	0.21	0.23	0.26	0.29	0.32	0.35	0.38	0.41	0.44	0.47	0.50	0.52	0.55	0.58	0.61	0.64	0.67
20 L/min	0.21	0.24	0.27	0.30	0.33	0.37	0.40	0.43	0.47	0.50	0.53	0.56	0.60	0.63	0.66	0.69	0.73
25 L/min	0.21	0.24	0.28	0.31	0.35	0.39	0.43	0.46	0.50	0.54	0.58	0.61	0.65	0.69	0.73	0.76	0.80
30 L/min	0.21	0.24	0.29	0.33	0.37	0.42	0.46	0.50	0.55	0.59	0.63	0.67	0.72	0.76	0.80	0.85	0.89
35 L/min	0.21	0.24	0.29	0.33	0.38	0.42	0.46	0.51	0.55	0.59	0.64	0.68	0.73	0.77	0.81	0.86	0.90
40 L/min	0.21	0.25	0.29	0.34	0.38	0.43	0.47	0.52	0.56	0.60	0.65	0.69	0.74	0.78	0.83	0.87	0.92
45 L/min	0.21	0.25	0.29	0.34	0.38	0.43	0.47	0.52	0.57	0.61	0.66	0.70	0.75	0.79	0.84	0.88	0.93
> 45 L/min	The FiO_2_ equals the oxygen concentration in the gas mixture																

Hudson mask or similar					
Oxygen flow	6 L/min	8 L/min	10 L/min	15 L/min	30 L/min
FiO_2_	0.45	0.50	0.54	0.59	0.65

Reservoir‐mask (non‐rebreather mask)	
Oxygen flow	≥ 10 L/min
FiO_2_	0.95

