### Registered Variables

2.10

The variables registered at baseline, daily during ICU admission, and at days 2, 4, and 90 are presented in Tables 3, 4, 5, respectively. Complete follow‐up during the 90‐day period for patients transferred to a non‐participating ICU or hospital will be obtained through mail or telephone contact.

**TABLE 3 aas70233-tbl-0003:** Baseline registrations.

Registration	Definition
Age	Calculated from birth date (years).
Sex	Legal sex, as defined by personal identification number in the Danish civil registration system (female/male).
Height	cm.
Weight	Absolute weight (kg).
Date of hospital admission	If transferred from a different hospital, the date of admission to the first hospital applies (ddmmyyyy).
Date and time of ICU admission	Date and time of admission to current ICU (ddmmyyyy, hh:mm).
Pre‐ICU location	(Emergency department or pre‐hospital setting/general ward/operating or recovery room/different ICU).
Surgery	Conducted during current hospitalisation (yes/no).
Surgery type^a^	Of last operation conducted (acute/elective).
Respiratory status	
Estimated pleural effusion size	Right and left side, measured between the parietal and visceral pleura perpendicularly to the chest wall at the largest separation point at randomisation (cm).
Type of respiratory support	At randomisation (Invasive ventilation/NIV including CPAP/oxygen on open systems).
Ventilator settings if invasively ventilated	FiO_2_ (fraction) at the time of the last ABG prior to randomisation, and peak pressure (cm H_2_O), tidal volume (ml) and positive end‐expiratory pressure (cm H_2_O) at the time of randomisation.
Ventilator settings non‐invasively ventilated (including CPAP)	FiO_2_ (fraction) at the time of the last ABG prior to randomisation, and end‐expiratory pressure (cm H_2_O) at randomisation.
If on open system	Type of system (nasal cannula/mask/non‐rebreather mask/T‐piece or speaking valve on tracheal cannula), flow (L/min) and fraction (decimal) of oxygen supplementation at the time of the last ABG prior to randomisation.
PaO_2_	Last ABG before randomisation (kPa).
SaO_2_	Last ABG before randomisation (%).
pH	Last ABG before randomisation.
PaCO_2_	Last ABG before randomisation (kPa).
p‐lactate	Highest plasma lactate measured in 24 h prior to randomisation (mmol/L).
Acute illness^b^	
Pneumonia^a^	As defined by clinicians and noted in the medical records (yes/no).

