#### Sample Size Calculation

2.14.1

To detect or reject an expected minimum of 75% relative increase (an absolute increase of 30% points) in patients receiving pleural drainage in the intervention group, and assuming a maximal incidence of pleural drainage in the ICU within 90 days of 40% in the control group, with a type 1 error risk (two‐sided α) of 0.05 and a type 2 error risk (*β*) of 0.20 (equal to a power of 80%), and an added 4 patients due to an expected dropout rate of maximum 5%, a total of 88 patients will be included. The trial is only powered to show relevant differences in the primary feasibility outcome; consequently, results in all secondary outcomes should be considered exploratory only.

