#### Outcome Analyses

2.14.3

The primary outcome will be analysed using a generalised linear model with a log‐link and Poisson data distribution according to the relation between variance and mean, and a robust variance estimation adjusted for the stratification variable trial site. Significance of the intervention will be assessed based on the *p*‐value from this regression and reported with the readily available risk ratio with 95% confidence interval. A *p*‐value below 0.05 will be considered statistically significant. A similar analysis, however, with an identity‐link and Poisson data distribution instead to produce the risk difference with 95% CI, will be conducted as well. Dichotomous secondary outcomes will be analysed similarly to the primary outcome; however, no *p*‐values will be reported given the lack of power and explorative nature of these outcomes. Continuous and ordinal secondary outcomes will be analysed using a generalised linear model with an identity‐link, Gaussian data distribution and a robust variance estimation, adjusted for the stratification variable trial site to produce a mean difference with 95% CI. A generalised linear model will be applied, regardless of expected non‐normal data distribution of the residuals. Similarly to the other secondary outcomes, no *p*‐values will be reported.

Additional per‐protocol sensitivity analyses will be conducted for all secondary clinical and process outcomes, excluding patients with one or more protocol violations as defined under secondary feasibility outcome (a).

For the secondary clinical outcome (e) proportion of patients with one or more serious adverse events, a supplemental analysis will be conducted in which death from any cause within 90 days will be included as a serious adverse event.

For the secondary clinical outcome (f) number of days alive without life support, a supplemental analysis will be conducted in which patients who die within 90 days will be assigned a value of 0 days alive without life support.

For the secondary process outcomes (i), (j), and (k), supplemental analyses will be conducted investigating differences in the PaO_2_:FiO_2_ ratio, PaCO_2_ and pH, respectively, between individual baseline and 72‐h measurements.

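### The blood-gas outcomes at 24 and 72 h are compared without adjusting for their recorded baseline values, which loses precision but does not bias the comparison

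*Protocol article*

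**What the plan says.** Outcome Analyses (2.14.3) sets one model for every continuous secondary outcome: identity link, Gaussian distribution, robust variance, "adjusted for the stratification variable trial site to produce a mean difference with 95% CI". Site is the only covariate. The three blood-gas measures, each taken from the arterial gas "conducted in ICU closest to 24 and 72 h after randomisation" (2.9.3), fall under this rule.

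Baseline appears in one further place in the same section: "supplemental analyses will be conducted investigating differences in the PaO_2_:FiO_2_ ratio, PaCO_2_ and pH", between each patient's baseline and 72-h values. Nothing comparable is planned for 24 h, and the covariates of this supplement are not stated.

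The baseline values are collected. Table 3 defines baseline PaO2 and PaCO2 as "Last ABG before randomisation (kPa"), takes pH from the same gas, and records the FiO2 or the open-system oxygen setting at that time. The note to Table 2 says the FiO2 conversion also serves baseline reporting. The article presents itself as the detailed statistical analysis plan, so the site-only model is a stated choice.

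**The concern.** Patients may enter on anything from supplemental oxygen in an open system to invasive ventilation, so gas exchange at entry is likely to vary widely. If a patient's later blood gas is related to the one before randomisation, a model that ignores the earlier value leaves that variation in the error term. It also lets a chance difference between the arms at baseline pass into the estimated effect.

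A change score is not an efficient remedy. It subtracts the whole baseline value, whatever the true slope of follow-up on baseline, and so over-corrects whenever that slope is below 1.

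What is at stake is the width of the intervals for three exploratory outcomes. The trial's stated aim includes preliminary outcome data to inform later trials, and for such estimates precision is most of their value.

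**Working it through.** **The plan's own figure.** The article gives no SD, correlation or target precision for the blood gases. Its only sample-size figure concerns the primary outcome: "assuming a maximal incidence of pleural drainage in the ICU within 90 days of 40% in the control group", "an absolute increase of 30% points", "with a type 1 error risk (two‐sided α) of 0.05", and 80% power. With a pooled variance and no continuity correction:

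n per arm = [1.960·√(2·0.55·0.45) + 0.842·√(0.40·0.60 + 0.70·0.30)]² / 0.30² = (1.379 + 0.565)² / 0.09 ≈ 42

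This gives 84 in total and, with the 4 added for dropout, 88. The stated figure reproduces and does not depend on the point made here.

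**Inputs for the blood gases.** The baseline/follow-up correlation r is an assumption, taken as 0.3, 0.5 and 0.7. The SDs at baseline and follow-up are assumed equal; the change-score formula needs this, the adjusted one does not.

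**Formulas.** Variance of the treatment contrast, relative to the planned follow-up-only model (= 1):
- baseline as covariate: 1 − r²
- change score: 2(1 − r)
- ratio of adjusted to change score: (1 − r²) / [2(1 − r)] = (1 + r)/2, which is below 1 for every r below 1

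| | r = 0.3 | r = 0.5 | r = 0.7 |
|---|---|---|---|
| Variance, baseline-adjusted | 0.91 | 0.75 | 0.51 |
| CI width, baseline-adjusted (square root) | 0.954 | 0.866 | 0.714 |
| CI narrower by | 5% | 13% | 29% |
| Variance, change score | 1.40 | 1.00 | 0.60 |
| Adjusted / change-score variance | 0.65 | 0.75 | 0.85 |

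**In SD units.** With 42 per arm, the 95% half-width is 1.96·√(2/42) = 0.43 SD for follow-up only. Baseline adjustment gives 0.41, 0.37 and 0.31; the change score gives 0.51, 0.43 and 0.33.

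**In patients.** If all 84 had a gas at the time point, adjustment would be worth an unadjusted trial of 84/0.91 ≈ 92, 84/0.75 = 112 or 84/0.51 ≈ 165 patients.

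**Chance imbalance.** The baseline difference between arms has a standard error of √(2/42) = 0.22 SD. A difference of d shifts the follow-up-only estimate by r·d and the change-score estimate by (r − 1)·d. At r = 0.5 and d = 0.22 SD, each moves by 0.11 SD, in opposite directions. Adjustment removes this component.

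**Check by simulation.** Normal data with four sites and site indicators, 3000 runs per setting, 42 per arm. Standard errors relative to follow-up only were 0.96, 0.87 and 0.72 for the adjusted model, and 1.18, 1.00 and 0.77 for the change score. With 25 per arm the adjusted ratios were 0.96, 0.88 and 0.72. The relative gain therefore persists when fewer patients still have an ICU gas, although every interval is wider.

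**The case against.** The strongest reply is that nothing here is wrong. Adjusting for the stratification variable alone is a valid prespecified choice, and follow-up-only and change-score contrasts estimate the same mean difference without bias under randomisation. The outcomes are secondary process measures, declared exploratory and reported without p-values. The gain rests on a correlation the article does not give: at 0.3 it is a 5% narrower interval. At 0.7 the planned supplement already recovers most of it at 72 h (variance 0.60 against 0.51). All of this stands, and it limits the weight of the point. It does not remove it, because the covariate is already collected and the supplement offers nothing at 24 h.

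A reader might also infer that the absence of a window in hours around 24 and 72 h lets a patient who leaves the ICU at 30 h supply one gas for both times, a hidden carry-forward. The document does not support that. Section 2.10 and Table 5 register these gases on days 2 and 4, and the note to Table 4 counts days from 06:00 to 06:00, starting at randomisation. On that count day 4 cannot begin before 48 h, so a gas at 30 h falls on day 2 or 3, and the natural reading is that the 72-h value is missing.

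**Conclusion.** The point holds as one of efficiency. The main models for PaO2:FiO2, pH and PaCO2 use site only, the baseline values are available, and the one analysis that uses them is a 72-h difference that is less precise than covariate adjustment at every correlation below 1 (given equal SDs). Below a correlation of 0.5 it is also less precise than ignoring baseline.

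The loss ranges from small (variance 0.91 of planned at r = 0.3) to substantial (0.51 at r = 0.7). It rests on the assumed correlation, and absolute precision also depends on how many patients still have an ICU blood gas. That the supplement is an unadjusted change score is the natural reading, though the text does not list its covariates.

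It would be too strong to conclude that the blood-gas comparisons are biased, that the primary result is affected, or that 88 patients is the wrong number. None of these follows.

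**What to change.** Before any data are analysed, state that the models for PaO2:FiO2, pH and PaCO2 at both 24 and 72 h include the patient's baseline value of the same measure alongside trial site. Keep the Gaussian identity-link model and robust variance.

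Then either replace the baseline-to-72-h supplement with this model or adjust the supplement for baseline too. The second option gives the same treatment estimate: if follow-up = a + τ·arm + b·baseline, then change = a + τ·arm + (b − 1)·baseline, with the same τ.

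The cost is an amendment to the analysis text. No new data are needed, and one parameter is added per model. A short rule is needed for any patient without a pre-randomisation gas, who would otherwise drop out of the adjusted model. The amendment should name the measures rather than their letters, since Outcome Analyses lists PaCO2 before pH and the outcome list has them the other way round. With 76 patients randomised by 11 March 2026 and the last expected in April 2026, the change should be dated and made public before analysis begins.

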#### Intervention Group

2.7.1

Patients in the intervention group will receive ultrasonography‐guided pleural drainage with insertion of a small‐bore catheter (typically pig‐tail type catheter, size 6–14 French) in the pleural cavity with pleural effusion of ≥ 2 cm as soon as possible, conducted by radiologists, intensivists, or surgeons, as per local standard. A time interval of up to 24 h from randomisation to intervention is expected to schedule pleural drainage and to allow for sufficient pausing of antithrombotic treatment or correction of coagulation deficiency if required. In case of bilateral pleural effusions ≥ 2 cm at randomisation, drainage of contralateral pleura will be conducted, expected within 24 h from insertion of the first pleural catheter. Inserted pleural catheters remain in situ and open until removed at clinicians' discretion according to local standards. If a new pleural effusion ≥ 2 cm is detected at any time during ICU stay within 90 days from randomisation, including during ICU readmissions, either contralaterally or ipsilaterally after pleural catheter removal, additional pleural drain insertion should be conducted.

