#### Secondary Feasibility Outcomes

2.9.1

Proportion of included patients with one or more protocol violations, defined as: (1) patients allocated to pleural drainage who do not receive pleural drainage within 24 h from randomisation, (2) patients allocated to pleural drainage with bilateral pleural effusion ≥ 2 cm, who do not receive the second (contralateral) pleural drainage within 24 h from the primary drainage unless pleural drainage has receded < 2 cm, and (3) patients allocated to no pleural drainage who receive pleural drainage at any time during ICU stay within 90 days from randomisation, including ICU readmissions, except when escape criteria for pleural drainage are present as specified (see Table 1).Recruitment proportion, defined as the proportion of included patients out of the number of eligible patients, i.e., patients who comply with all inclusion and exclusion criteria over the duration of trial inclusion.Proportion of recruited patients with consent withdrawn for the use of data

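### The per-protocol set drops intervention patients who die, leave the ICU or improve undrained within 24 h but keeps their control counterparts, so the per-protocol contrasts can be biased in either direction

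*Protocol article*

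**What the plan says.** Section 2.14.3 (Outcome Analyses) plans a per-protocol version of the results and gives its scope: "sensitivity analyses will be conducted for all secondary clinical and process outcomes". Membership of that set is then fixed by this rule: "excluding patients with one or more protocol violations as defined under secondary feasibility outcome (a". The per-protocol set is thus built directly from the violations listed in section 2.9.1 (Secondary Feasibility Outcomes):

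- **Violation (1), intervention arm:** "patients allocated to pleural drainage who do not receive pleural drainage within 24 h from randomisation". No exception is attached.
- **Violation (2), intervention arm:** in bilateral effusion, no second-side drainage within 24 h of the first, "unless pleural drainage has receded < 2 cm". The word drainage here is evidently a slip for effusion.
- **Violation (3), control arm:** "patients allocated to no pleural drainage who receive pleural drainage at any time during ICU stay within 90 days from randomisation", except when an escape criterion is present.

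Section 2.7.1 (Intervention Group) allows up to 24 h between randomisation and drainage, partly "to allow for sufficient pausing of antithrombotic treatment or correction of coagulation deficiency if required". Section 2.14.2 makes intention to treat the population for all analyses. Section 2.14.1 declares all secondary outcomes exploratory, and section 2.14.3 reports them without p-values.

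**The concern.** A patient in the intervention arm can die, be discharged from the ICU or have the effusion recede during the hours allowed for arranging drainage. If that happens before a catheter is placed, violation (1) applies and the patient leaves the per-protocol set. A control patient with the identical course has violated nothing and stays. Intervention patients must therefore survive, remain in the ICU and keep an effusion until drained, while control patients face no such condition.

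The set covers 90-day mortality, serious adverse events, days alive without life support, days alive and out of hospital, and the blood-gas outcomes at 24 and 72 h. Removing the sickest or the fastest-improving patients from one arm can shift any of these without a treatment effect. A reader would normally take agreement or disagreement between the per-protocol and intention-to-treat results as informative. Here part of any difference could come from the exclusion rule alone.

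The rules are also inconsistent with each other: a receded effusion excuses a missed second drainage but not a missed first one.

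**Working it through.** **Who is removed, by early course (undrained in the first 24 h)**

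- Dies: removed if intervention (violation 1), kept if control.
- Leaves the ICU: removed if intervention, kept if control.
- Effusion falls below 2 cm: removed if intervention, kept if control.

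Violation (3) does not balance this. It removes control patients who were drained outside the escape criteria, which is a different event.

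**Arm size.** The plan's total reproduces. For 40% versus 70%, two-sided alpha 0.05 and 80% power, with pooled variance and no continuity correction:

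n = [1.96 × √(2 × 0.55 × 0.45) + 0.842 × √(0.40 × 0.60 + 0.70 × 0.30)]² / 0.30² = 41.97, so 42 per arm. Then 2 × 42 + 4 = 88, or 44 per arm. The concern does not depend on this figure; it only supplies the scale.

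**Size of the artefact under no treatment effect.** The protocol gives no mortality or early-event rates, so these inputs are assumed:

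- m = 90-day mortality in both arms, 35% (30% and 40% as a check)
- a = share of the intervention arm dying undrained within 24 h
- b = share leaving the ICU or improving undrained within 24 h
- mb = 90-day mortality of that second group, 10%

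Per-protocol mortality in the intervention arm = (m − a − b × mb) / (1 − a − b). Control mortality is held at m, so exclusions under violation (3) are left out.

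*Early deaths only (b = 0), m = 35%*
- a = 2%: 0.33 / 0.98 = 33.7%; RR 0.96
- a = 4%: 0.31 / 0.96 = 32.3%; RR 0.92
- a = 6%: 0.29 / 0.94 = 30.9%; RR 0.88

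Of 44 patients, 2% to 6% is about 1 to 3.

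*Early leavers or improvers only (a = 0), m = 35%*
- b = 5%: (0.35 − 0.005) / 0.95 = 36.3%; RR 1.04
- b = 10%: (0.35 − 0.01) / 0.90 = 37.8%; RR 1.08
- b = 20%: (0.35 − 0.02) / 0.80 = 41.3%; RR 1.18

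*Both, m = 35%*
- a = 4%, b = 10%: (0.35 − 0.04 − 0.01) / 0.86 = 34.9%; RR 1.00

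*Wider range*
- m = 30%, a = 10%, b = 0: 0.20 / 0.90 = 22.2%, a shift of −7.8 points
- m = 40%, a = 0, b = 20%: 0.38 / 0.80 = 47.5%, a shift of +7.5 points

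**Effect of the remedy.** If these patients are kept in both arms, mortality is 35% versus 35%. With a 24-h landmark in both arms and a = 4%, it is 32.3% versus 32.3%. The artefact is zero either way.

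**The case against.** **Scope.** A reader might infer that the trial's clinical comparisons are biased. The documents do not support that. The clinical comparisons are by intention to treat, the primary outcome has no per-protocol analysis, and the affected results are exploratory and carry no p-values. This objection stands and limits the point to the per-protocol sensitivity analyses.

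**Direction.** It is tempting to call this an immortal-time advantage for drainage. That holds for early deaths alone. Leavers and improvers push the other way, and plausible mixtures cancel. No direction is established.

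**Coagulation delays.** A reader might also infer that section 2.7.1 expects patients needing antithrombotic pauses or correction to overrun, so that higher-risk patients are systematically excluded. The text places that interval within 24 h, which is the violation limit itself. Exclusion criterion (6) also removes patients whose coagulation problem cannot be reversed. Some delay beyond 24 h remains possible, but the documents give no rate for it.

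**Few cases.** Exclusion of patients with an expected ICU stay under 24 h or imminent withdrawal of therapy will make early deaths and exits rarer. Both are forecasts at entry, so they do not remove such cases.

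**Size against noise.** At 44 per arm and 35% mortality, the standard error of the log risk ratio is √(2 × 0.65 / (44 × 0.35)) = 0.29. A null 95% interval is then about 0.57 to 1.77, far wider than the shifts shown. This is a fair reason not to overrate the issue. It does not justify a set that selects one arm when the remedy is a sentence.

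**Purpose of violation (1).** Counting every undrained patient is defensible for a feasibility measure of delivery within 24 h. That stands, and the feasibility outcome should be left alone.

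**Conclusion.** The point holds for the per-protocol sensitivity analyses. As written, the rule removes intervention patients for early death, ICU exit or a receded effusion, and never removes comparable control patients. The resulting contrasts can be shifted in either direction without a treatment effect.

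With an assumed 35% mortality, the risk ratio runs from 0.96 to 0.88 for 2% to 6% early undrained deaths alone. It runs from 1.04 to 1.18 for 5% to 20% early leavers or improvers at an assumed 10% mortality, and is close to 1 in some mixtures. All these rates are assumptions, and control exclusions under violation (3) are not modelled, so the net bias in this trial is unknown.

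It would go too far to call the per-protocol analyses uninterpretable. They need a symmetric rule for these early events and a stated limitation for what remains.

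**What to change.** - **Per-protocol set only (section 2.14.3):** state that intervention patients who died, left the ICU or had the effusion recede below 2 cm undrained within 24 h of randomisation are not excluded. Leave feasibility outcome (a) unchanged, because editing violation (1) itself would alter that outcome.
- **Alternative:** start the per-protocol analysis from a common 24-h landmark, alive and in the ICU, in both arms. The allowance for a receded effusion would still be needed, since such a patient can be alive and in the ICU at 24 h. Table 5 lists a date of death without a clock time, so timing would have to be confirmed for deaths near the limit.
- **Violation (2):** replace the word drainage with effusion in the exemption.
- **Data:** record the reason for non-drainage. Table 4 as published captures the indication for each drainage but neither a reason for its absence nor daily effusion size.
- **Limitation:** state that selection remains from drainage delayed beyond 24 h, which neither option removes. As an illustration, suppose 8% are delayed and have 60% mortality (both assumed). Even with the exemption, per-protocol mortality is (0.35 − 0.048) / 0.92 = 32.8% versus 35%, RR 0.94.

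The cost is a few lines of text, one query per undrained intervention patient and a slightly less strict per-protocol set. Section 4.1 reports 76 of 88 patients randomised by 11 March 2026, and section 3.1 places publication of the plan before any data analysis. A change made before analysis would still count as prespecified.
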